# Evaluation of the Intensive Treatment and Rehabilitation Program for Residential Treatment and Rehabilitation Centers (INTREPRET) in the Philippines: a study protocol for a randomized controlled trial

**DOI:** 10.1186/s13063-021-05882-6

**Published:** 2021-12-11

**Keywords:** Methampetamine use disorders, Cognitive-behavioral therapy, The Philippines, Residential treatment, Therapeutic community, Matrix Model

## Abstract

**Background:**

The Philippines has been severely affected by the methamphetamine crisis. The government has launched a policy war against drug use, although the severe sanctions imposed on drug users have been criticized internationally. To help implement a more effective and humane approach to drug use, this study aimed to introduce a comprehensive treatment program for methamphetamine users based on cognitive-behavioral therapy (CBT) whose effectiveness will be evaluated through a randomized controlled trial.

**Methods:**

Methamphetamine users admitted into government-run rehabilitation facilities are recruited and randomly assigned to either a CBT-based treatment program or existing therapeutic community (TC)-based treatment. The CBT treatment program was developed based on the Matrix Model that considers cultural and social factors in the Philippines. After 6 months of treatment, there will be a three-month follow-up, when the participants’ drug use (tested through urine testing) and other psychological variables, including craving, coping skills, and well-being, will be compared. Potential participants are given a summary of the study and a consent form. The consent form is signed and dated by participants prior to their study participation. Ethical approval was obtained prior to the commencement of the study.

**Discussion:**

This is the first randomized controlled trial to compare the residential CBT program and the TC model for methamphetamine users in the Philippines. The study aims to fill the current knowledge and capacity gaps by introducing a CBT-based treatment program to improve the psychosocial well-being of drug users in the Philippines. Moreover, if the effectiveness of the treatment program is demonstrated, anti-drug campaigns and severe sanctions against drug users may be reconsidered.

**Trial registration:**

UMIN Clinical Trials Registry JPRN-UMIN000038597. Registered on 15 November 2019. Protocol version October 17, 2021 ver.2

## Background

### Introduction

The crisis in methamphetamine use has spread worldwide in recent times, particularly in Southeast Asia, with methamphetamine seizures in the region reaching 1000 tons in 2018, which was five times larger than that in 2013 [1]. The Philippines is one of the most severely affected countries in this region, where drug use has become a major public health concern. National statistics indicated a prevalence rate of illegal drug use in 2.3% of the population in 2015 or the equivalent of 1.8 million people in the 10–69 years age range [2].

Under these circumstances, President Rodrigo Duterte declared a war on drugs and launched a national anti-drug campaign in 2016, involving dismantling clandestine methamphetamine laboratories and arresting drug suppliers [3]. Over one million drug users made themselves known to the authorities and sought treatment and social support [4]. This unprecedented demand for drug use treatment services highlighted knowledge and capacity gaps in existing services. Therefore, there is an urgent need to develop evidence-based treatment that considers the country’s cultural and social background. It is estimated that 1% of those who came forward were high-risk users [5], who usually have multiple and intensive treatment needs.

The Philippine Department of Health is responsible for providing residential treatment for high-risk drug users and operates 12 treatment and rehabilitation centers (TRCs) nationwide. They rely heavily on a therapeutic community (TC) model, which is very popular. However, no robust evaluation has been undertaken of this model, and there is wide variability in practice. Furthermore, one meta-analysis did not identify any significant benefits for the rehabilitation of drug users using that model [6]. Additionally, the TC model employed in the TRCs varies. Its major elements include group meetings, religious gatherings, physical exercise, and housekeeping activities. These elements are usually delivered for 6 months in an unstructured manner and their effectiveness remains unevaluated.

Cognitive-behavioral thearpy (CBT) is commonly used to treat individuals with drug problems worldwide and is popular in Western countries. However, there is no clear evidence for its effectiveness in treating methamphetamine use disorders in terms of high-quality research [7]. CBT addresses multiple treatment needs of drug users, including building skills to resist drug use, replacing drug-using activities with constructive and rewarding activities, improving problem-solving skills, and facilitating better interpersonal relationships in a structured manner [8, 9].

The Matrix Model is a specifically designed CBT-based treatment model to treat stimulant users and has been evaluated many times in several countries, such as the USA [10–12] as well as Asian countries, including Japan [13] and Iran [14]. We developed a comprehensive CBT treatment program based on the Matrix Model considering Philippine cultural and social factors, to treat methamphetamine users in TRCs, namely, an “Intensive Treatment and Rehabilitation Program for Residential Treatment and Rehabilitation Centers” (INTREPRET).

### Aims and objectives

This study aimed to fill knowledge and capacity gaps through introducing INTREPRET into the Philippines and comparing it with current TC-based treatment, through conducting a parallel group randomized controlled trial to evaluate its effectiveness concerning subsequent drug use and psychosocial well-being. The primary objectives of this study are:
To establish an evidence-based residential treatment model for national dissemination. The findings of the study are expected to bring long-term benefits to high-risk drug users and communities alike through determining whether this treatment model works in the Philippine residential setting or needs further improvement before it is scaled up nationwide.To direct policymakers towards the introduction of more effective treatment, to contribute to improved treatment services for drug users, and to facilitate approaches more respectful of drug users’ human rights and dignity.

## Methods

### Overview

The trial design is a parallel group randomized control trial. The study protocol was developed by the authors (chaired by the first author) following the CONSORT Statement [15] and the Standard Protocol Items: Recommendations for Interventional Trials (SPIRIT) [16]. The protocol, research method, and collected data have been checked and overseen by a Research Working Group (RWG) headed by the program manager of the Philippine Dangerous Drugs Abuse and Prevention and Treatment Program (DDAPTP). The RWG is composed of both Japanese and Philippine researchers, including the authors of this protocol, and responsible for auditing core trial processes.

### Study setting

INTREPRET will be introduced into three Department of Health-operated TRCs, selected as representative in terms of patient and facility characteristics, to ensure external validity.

### Participant enrolment and allocation

The participants are recruited from among newly admitted patients in three TRCs starting from April 2022; the process will continue for approximately three years until the total number of participants from those TRCs reaches 400. We are in close contact with the staff in charge of recruiting to monitor the enrolment process.

Those who meet the eligibility criteria are selected as participants for the study. After obtaining informed consent, participants are randomly assigned to either the intervention group or the control group. During the intervention phase, the patients in the intervention group will receive INTREPRET, while those in the control group will receive current TC-based treatment or treatment as usual (TAU).

Randomization of eligible patients is performed by independent research assistants who are not part of the TRC administration. When a new eligible patient is admitted to the TRCs, the staff inform the allocation team, and the patient is randomly assigned to either of the groups using a pre-determined computer-generated table. The table has a block size of 20 with ten intervention and ten control statuses listed in a random sequence. A new table is generated and used in every 20 newly admitted patients. The tables are placed in a sealed envelope and retained by the data collection team in locked storage until the end of the trial.

The blinding of participants in terms of interventions they receive cannot be ensured because of the nature of the intervention. However, research assistants responsible for recruiting participants, and data collection and analysis are adequately blinded.

### Eligibility criteria

The following inclusion criteria apply:
Residential patients newly admitted to one of the three pilot TRCsBeing maleBeing 18 years of age or olderEver having used methamphetamine

The following exclusion criteria apply:
Those not capable of participating in group sessionsThose who cannot communicate in TagalogThose with criminal records other than for possession of illegal drugs, possession of drug paraphernalia, or use of illegal drugsThose with severe medical conditions

Participation is limited to males because the overwhelming majority of drug users are male, so their clinical needs have a high priority. The patients in the intervention group are separated from those in the control group (and those not participating in the study) by placing them in a designated dormitory to avoid possible between-group communication. They are also instructed not to disclose treatment materials to non-intervention group participants. No specific dormitories are designated for the control group, whose participants stay in non-intervention group dormitories together with those not participating in the study.

While allowing for dropout or withdrawal, data are still collected for intention-to-treat analysis for all dropout/withdrawal cases. The following dropout/withdrawal criteria apply:
Explicit statement of intent to reject receiving treatmentExplicit statement of withdrawal from study participationFailure to receive treatment more than 5 timesFailure to comply with institutional regulations

### Sample size calculation

Based on recently published findings from a systematic review that included studies with a similar design [7], this study considered a minimum detectable effect of 0.23 and a population standard deviation of 0.42. With a significance level of 0.05, and a power of 0.95, a sample size of 88 participants per group (or 176 patients in total) was determined as needed to test the causal effect of the intervention.

Based on preparatory field study experience, it is possible that more than half of the participants may drop out of the study by not showing up for the follow-up interviews in the three months after discharge. Given a coverage rate of 44%, the final required sample size needed to be adjusted to 200 patients per group (or 400 patients in total) to achieve a sample size of 88 patients per group (or 176 patients in total).

### Intervention

The original Matrix Model was translated into the Tagalog language, and local researchers and practitioners checked the translation multiple times. Additionally, the contents were tailored to the cultural and social background of the Philippines and specific treatment needs of drug users in the Philippines and modified to be conducted in residential TRC settings.

INTREPRET is composed of five components: CBT sessions, CBT-review sessions, psycho-education sessions, social support sessions, and self-help group meetings. The main contents of the CBT sessions are as follows: (1) identifying triggers for drug use, (2) learning coping skills for triggers, (3) learning alternative behaviors, (4) learning coping skills for craving, (5) learning coping skills for negative emotions (anger management, stress management), and (6) rebuilding social support networks.

To implement these five components of INTREPRET, the following materials have been developed:
A service provider manual [17]A patient workbookSlides for psycho-education sessionsFlipcharts for social support sessions

In implementing INTREPRET, service providers follow the protocols described in the manual [17], which elaborates the organization and resource requirements for the implementation of different treatment components and the use of specific materials and tools. It also provides operating procedures and quality standards to facilitate group sessions for each treatment component.

During the intervention, the patients in the intervention group receive INTREPRET through participating in three sessions of CBT, one session of CBT review, one session of psycho-education, two sessions of social support, and one session of self-help group meetings per week. All sessions, each lasting 60 min, are provided in groups. INTREPRET can be completed within 26 weeks or 6 months. Other than these CBT interventions, participants join other TC-based activities, such as physical activities and religious gatherings. Table 1 shows a sample timetable with INTREPRET program components incorporated into the TC-based treatment platform.

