### Data analysis

The following two types of regression equations are estimated to calculate the causal effect of providing residential treatment on outcomes:
For the primary outcome indicator of urine testing, regression model (1) was estimated to test any statistically significant difference in means between the intervention and control groups:

1$$ {Y}_{ij}=\alpha +\beta {T}_i+\theta {X}_i+{v}_j+{\omega}_{ij} $$

where *Y*_*ij*_ is the urine test result of patient *i* at TRC *j*, *α* is a constant that gives the value of the urine test result for the control group, *T*_*i*_ is the treatment dummy, *X*_*i*_ is the set of patient characteristics to be controlled for, such as age and education, *v*_*j*_ is a TRC-level error term, and *ω*_*ij*_ is an individual error term.

This study estimates the coefficient of the treatment dummy (*β*), which shows the between-group difference. Since the urine test has a binary result, the log odds of the outcome are to be estimated as a linear combination of the independent variables using logistic regression (i.e., logit (*Y*_*ij*_)) rather than linear regression.
2)For the secondary outcome indicators of the psychometric tests, which are to be measured both at baseline and follow-up, regression model (2) with an interaction term is estimated to calculate a difference-in-difference (DD) estimate that relies on a comparison of the intervention and control groups before and after the intervention [29]:

2$$ {Y}_{ijt}=\alpha +\beta {T}_{i1}t+{\rho T}_{i1}+\gamma t+\theta {X}_i+{v}_{jt}+{\omega}_{ijt} $$

where *Y*_*ijt*_ is the psychometric test result of patient *i* at TRC *j* at time *t*, *α* is a constant giving the average value of the psychometric test result for the comparison group at time *t*_0_ (baseline), *T*_*i*1_ is the treatment dummy, *t* is the time dummy, *X*_*i*_ is the set of patient characteristics to be controlled for, *v*_*j*_ is a TRC-level error term, and *ω*_*ij*_ is an individual error term.

The study estimates the coefficient (*β*) on the interaction between the treatment dummy (*T*_*i*1_) and the time dummy (*t*), which gives the average DD effect of the intervention. In addition to this interaction term, the variables *T*_*i*1_ and *t* are included separately to identify any separate mean effects of time as well as the effect of being targeted versus not being targeted.

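### INTREPRET is delivered entirely in groups, but neither the written models nor the 88 per group allows for correlation within the intervention arm, so the standard error of the treatment effect is understated if any exists

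*Protocol article*

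**What the plan says.** Patients are randomised individually, 1:1 (Participant enrolment and allocation): "The table has a block size of 20 with ten intervention and ten control statuses listed in a random sequence".

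The Intervention section gives the INTREPRET arm eight weekly sessions (3 CBT, 1 CBT review, 1 psycho-education, 2 social support, 1 self-help), in a programme that can be completed in 26 weeks. On delivery it says: "All sessions, each lasting 60 min, are provided in groups".

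Eligibility criteria adds that intervention patients are kept apart "by placing them in a designated dormitory to avoid possible between-group communication". Controls have no dormitory of their own and live among patients outside the study.

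Data analysis writes both models out. In model (1), v_j "is a TRC-level error term, and" ω_ij is an individual error. Model (2) has the same two levels, indexed by time. Neither has a term for therapy group, dormitory or therapist.

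Sample size calculation uses "a minimum detectable effect of 0.23 and a population standard deviation of 0.42". "With a significance level of 0.05, and a power of 0.95", it arrives at 88 per group, raised to 200 per group for 44% follow-up. It mentions no ICC, group size or design effect, and has no TRC component.

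**The concern.** Patients treated and housed together share facilitators, peer influence and local events, so their outcomes may be correlated. Here that structure is asymmetric. It is created by treatment in one arm, while patients were randomised one at a time. This is the partially nested design.

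The TRC term looks as if it might deal with this, but it does not. Both arms are present in each TRC, so v_j is common to both and largely cancels from β. A group effect that exists only on the INTREPRET side goes straight into β. A model without that level treats the variation as independent noise and reports too small a standard error.

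The nominal 5% test then rejects too often, and an analysis that did allow for the correlation would have less than the planned power. The result is meant to inform national dissemination, so evidence overstated in this way matters. Group membership that is not recorded during the trial may be impossible to recover afterwards.

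**Working it through.** **Inputs from the protocol article.** Difference 0.23, SD 0.42, alpha 0.05, power 0.95, 88 analysed and 200 enrolled per group, 44% follow-up, three TRCs, about three years of recruitment, about six months of treatment. **Assumed, because not given:** ICC 0.01 to 0.10, and analysed patients per cluster m.

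**Step 1. Reproduce the plan's figure.** n = 2(1.960 + 1.645)² × 0.42² / 0.23² = 86.7, so 87 by the normal approximation. The t-based version gives 87.6, so 88. A one-sided test would give 73, which does not match. Then 88 / 0.44 = 200. Power at 88 per group is Φ(0.23 / (0.42√(2/88)) − 1.960) = Φ(3.632 − 1.960) = 0.953. The stated figure is therefore a two-sided comparison of independent patients, with no hidden allowance for clustering.

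**Step 2. What group size fits the planned flow?** 200 intervention patients over 36 months in three TRCs is 200/(36 × 3) = 1.85 per TRC per month, assuming equal sites. Over a six-month stay that is about 11 in residence at once. A group of 10 enrolled leaves 10 × 0.44 = 4.4 analysed. A closed group with 8 analysed needs 8/0.44 = 18.2 enrolled, or 18.2/1.85 = 9.8 months of a TRC's intake. So m = 8 is more plausible for open groups with turnover than for closed cohorts.

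**Step 3. Clustering in the intervention arm only.** Design effect in that arm: DE = 1 + (m − 1) × ICC. Ratio of true to assumed variance of the difference: VR = (DE + 1)/2. Then the SE ratio is √VR, type I error is 2[1 − Φ(1.960/√VR)], and power is Φ(3.632/√VR − 1.960).

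| m | ICC | DE | SE ratio | Type I error | Power |
|---|---|---|---|---|---|
| 4.4 | 0.02 | 1.07 | 1.02 | 0.054 | 0.947 |
| 4.4 | 0.05 | 1.17 | 1.04 | 0.060 | 0.937 |
| 4.4 | 0.10 | 1.34 | 1.08 | 0.070 | 0.919 |
| 8 | 0.01 | 1.07 | 1.02 | 0.054 | 0.946 |
| 8 | 0.05 | 1.35 | 1.08 | 0.071 | 0.918 |
| 8 | 0.10 | 1.70 | 1.16 | 0.092 | 0.878 |
| 29.3 | 0.01 | 1.28 | 1.07 | 0.067 | 0.925 |
| 29.3 | 0.02 | 1.57 | 1.13 | 0.084 | 0.894 |
| 29.3 | 0.05 | 2.42 | 1.31 | 0.134 | 0.794 |

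The rows with m = 88/3 = 29.3 treat one dormitory per TRC as the cluster for the whole recruitment period. That is a strong assumption, because its residents change. All power figures use a normal critical value. With few clusters, a small-sample correction would lower them further.

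**Step 4. Check by simulation.** A logistic model with TRC terms was fitted to 88 per arm, with no treatment effect and group effects in the intervention arm only (1,500 runs per setting, ICC on the logit scale). Rejection rates at nominal 0.05 were:
- ICC 0: 0.055.
- Three groups per TRC (about 10 per group), ICC 0.05 and 0.10: 0.073 and 0.095.
- One cluster per TRC, ICC 0.02, 0.05 and 0.10: 0.081, 0.104 and 0.175.

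The TRC terms were in the model and did not remove the inflation.

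**Step 5. Cost in patients.** For 95% power with m = 8, n = 86.7 × VR. ICC 0.05 gives 86.7 × 1.175 = 102 analysed (102/0.44 = 232 enrolled) per group. ICC 0.10 gives 86.7 × 1.35 = 117 analysed (117/0.44 = 266 enrolled).

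**The case against.** The strongest reply is that the size rests wholly on assumed values. The article gives no ICC. The primary outcome is a urine test three months after treatment, when patients have left the groups and dormitory, and aftercare is offered to everyone. A small ICC is quite possible. At ICC 0.01 to 0.02 with small groups the standard error is off by about 2% or less, and the planned 95% power leaves room. This stands, and it limits how firmly the size can be stated.

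It can also be said that a condensed article leaves variance estimation to the analysis plan. That stands only in part. The article does not say how standard errors are computed, but it does write out the error structure of both models, and the therapy-group level is absent from it.

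A reader might infer more than the documents support:
- That patients spend 26 weeks with the same peers and facilitator. Nothing says the groups are closed, and individual enrolment over about three years points to rolling entry.
- That sessions take place in the dormitory. The text concerns housing only.
- That type I error is 8 to 13%. For therapy groups this needs 9 to 15 analysed patients per group with ICC 0.05 to 0.10. A closed group with 9 analysed would use 9/0.44/1.85, about 11 months, of a TRC's intake; one with 15 would use about 18 months.
- That power falls to 0.85 or 0.80, as it does at 50% versus 27% positive tests with about 9 per group. Those rates are not in the article, and power at them is already 0.897 with no clustering. At ICC 0.05, about half of the fall from 0.95 to 0.846 comes from the changed rates.

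Finally, controls attend TC meetings and also share dormitories, so treating them as fully independent is itself an assumption. If they cluster equally, the understatement grows: at m = 8 and ICC 0.05, type I error is 0.092 and power 0.878.

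**Conclusion.** The point holds in direction and is conditional in size. The design creates a clustering level in the intervention arm that both written models and the sample size leave out, and the TRC term does not replace it. For any positive within-group ICC, the model-based standard error of β is too small.

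With group sizes that fit the planned patient flow, the inflation is modest: type I error about 0.054 to 0.070. With 8 analysed per group and ICC 0.05 to 0.10 it becomes material. If one dormitory per TRC acts as the cluster, even ICC 0.02 matters.

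The main harm is to standard errors and the false-positive rate. Loss of power is secondary. The documents do not support saying that the error bars are certainly too narrow by a given amount, because neither ICC nor group size is stated.

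**What to change.** 1. **Record membership prospectively.** For each intervention patient, record therapy group, entry and exit dates, and facilitator. For controls, record the TC group if there is one.
2. **Model it.** Add an intervention-arm group effect to models (1) and (2), with a small-sample correction. Use a partially nested effect if groups are closed, or a multiple-membership effect if they are open. If controls also have identifiable groups, nest them in those.
3. **Plan for the case where the effect cannot be estimated.** If each TRC has only one rolling group or one dormitory, that level coincides with TRC-by-arm, and three clusters cannot support a reliable variance estimate. Report instead a sensitivity analysis of the interval for β over a stated ICC range. Adding patients alone would not cure clustering at this level.
4. **Restate power.** In Sample size calculation, say that 0.95 holds only at ICC 0, and give power over a range of ICC and group size, as in the table above.

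The cost is a few recorded fields, a slightly wider interval and a lower stated power. Open groups make the model somewhat more complex than one extra term. Treatment delivery does not change.
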